# Treatment with L-citrulline in patients with post-polio syndrome: study protocol for a single-center, randomised, placebo-controlled, double-blind trial

**DOI:** 10.1186/s13063-017-1829-3

**Published:** 2017-03-09

**Keywords:** L-citrulline, Post-polio syndrome, Clinical trial, Quantitative MRI

## Abstract

**Background:**

Post-polio syndrome (PPS) is a condition that affects polio survivors years after recovery from an initial acute infection by the Poliomyelitis virus. Most often, patients who suffered from polio start to experience gradual new weakening in muscles, a gradual decrease in the size of muscles (muscle atrophy) and fatigue years after the acute illness. L-citrulline is known to change muscular metabolism synthesis by raising nitric oxide (NO) levels and increasing protein synthesis. This investigator-initiated, randomised, placebo-controlled, double-blind, trial aims to demonstrate that L-citrulline positively influences muscle function and increases muscular energy production in patients with PPS.

**Methods/design:**

Thirty ambulant PPS patients will be recruited in Switzerland. Patients will be randomly allocated to one of the two arms of the study (placebo:verum 1:1). After a 24-week run-in phase to observe natural disease history and progression, participants will be treated either with L-citrulline or placebo for 24 weeks. The primary endpoint is change in the 6-min Walking Distance Test. Secondary endpoints will include motor function measure, quantitative muscle force, quantitative muscle magnetic resonance imaging and magnetic resonance spectroscopy and serum biomarker laboratory analysis

**Discussion:**

The aim of this phase IIa trial is to determine if treatment with L-citrulline shows a positive effect on clinical function and paraclinical biomarkers in PPS. If treatment with L-citrulline shows positive effects, this might represent a cost-efficient symptomatic therapy for PPS patients.

**Trial registration:**

ClinicalTrial.gov, ID: NCT02801071. Registered on 6 June 2016.

**Electronic supplementary material:**

The online version of this article (doi:10.1186/s13063-017-1829-3) contains supplementary material, which is available to authorized users.

## Background

### Poliomyelitis and post-polio syndrome (PPS)

Poliomyelitis is an infectious viral disease that can strike at any age and affects the nervous system, resulting in paralysis with muscle spasms and, in some cases, acute encephalitis [1]. To date, most regions in the world are certified polio free. However, poliomyelitis is still endemic in two countries worldwide (Afghanistan and Pakistan) with 74 reported cases in 2015 [2].

PPS is a condition that affects polio survivors years after recovery from an initial acute infection by the Poliomyelitis virus. Most often, patients affected by polio start to experience gradual new weakening in muscles which were previously infected by the original polio infection [1].

The most common symptoms include slowly progressive muscle weakness, fatigue (both generalised and muscular) and a gradual decrease in muscle size (muscle atrophy). The diagnosis of PPS relies nearly entirely on clinical information. Physicians diagnose PPS after completing a comprehensive medical history and physical examination, and by excluding other disorders that could explain the symptoms [3].

The exact incidence and prevalence of PPS is unknown. Due to the large number of polio survivors, in 2004 250,000 patients with PPS were estimated in Europe, 20 million worldwide [4]. Ragonese et al. showed in 2005 a prevalence rate for PPS of 31% (women more than men) in patients affected by poliomyelitis [5].

The aetiology and pathogenesis of PPS are unclear. It has been hypothesised that the new weakness of PPS appears to be related to the degeneration of individual nerve terminals in the motor units. The usage of these recovered but overly extended motor units for years overstresses the neurons which, over time, lose their ability to maintain the increased work demands. This results in slow deterioration of the neurons, leading to reduced muscle strength [6, 7].

This hypothesis explains why PPS occurs after a delay and has a slow and progressive course. There are currently no effective pharmaceutical or rehabilitative treatments that can stop the deterioration or reverse the deficits caused by the syndrome itself [8].

### L-citrulline

L-citrulline (CIT) is a nonessential amino acid, not involved in protein synthesis. However, CIT plays a central part in cellular metabolism. CIT is produced but not metabolised in the gastrointestinal tract. More than 80% of the citrulline produced by the gastrointestinal tract appears to be taken up by the kidneys [9, 10]. CIT is then converted to L-arginine in the renal proximal tubules (via the enzymes arginosuccinate synthase and arginosuccinate lyase) [9]. As a precursor of L-arginine, CIT is transformed into nitric oxide (NO) by nitric oxide synthase (NOS). El-Hattab et al. demonstrated that the intake of CIT in MELAS (mitochondrial encephalomyopathy, lactic acidosis, and stroke-like episodes) patients showed a substantially higher increase of L-arginine and NO plasma concentrations than did the same dose of L-arginine [11]. Both CIT and L-arginine support NO synthesis in a variety of tissues, including muscle tissue. Osowska et al. reported that with a CIT-enriched diet, protein synthesis improved and, therefore, the protein mass in the muscle could be increased [12]. NO triggers mitochondrial biogenesis and enhances coupled respiration and adenosintriphosphate (ATP) production. This process is mediated via a cGMP (guanosine 3’,5’-monophosphate)-dependent signalling pathway that activates the expression of peroxisome proliferator-activated receptor-γ coactivator 1α (PGC-1α), which is a master regulator of mitochondrial biosynthesis [13].

Therefore, CIT supplementation results in reduced fatigue and improved endurance for both aerobic and anaerobic prolonged exercise. It seems to interact with ATP production (in a beneficial manner) by increasing the efficiency of energy production [14].

Single oral doses of CIT of up to 15 g are tolerated without any side effects in contrast to equivalent oral doses of L-arginine, where osmotic diarrhoea has been observed [15]. The same observations may be reported in our own studies (data not yet published) in which CIT (doses of up to 15 g/d) was administered to patients with Becker muscular dystrophy and Duchenne muscular dystrophy.

Unpublished results showed beneficial effects of CIT on muscle function and fatigue in muscular dystrophies. In both pathways, the stimulation of skeletal muscle protein syntheses via ATP production and mitochondrial biosynthesis stimulation could be potentially useful in other chronic neuromuscular disorders of neurogenic origin such as PPS.

## Methods/design

### Study design

The study is an investigator-initiated, randomised, placebo-controlled, double-blind, efficacy phase IIa trial and is conducted over a time period of 48 weeks. We plan to enrol 30 ambulant PPS patients aged older than 18 years. Recommendations for Interventional Trials (SPIRIT) Checklist on which the study protocol is based is presented as Additional file 1. A (SPIRIT) figure, showing the planned visit and examination schedule is presented in Fig. 2.﻿

### Inclusion criteria

In order to participate, patients are required to meet the following criteria:

be ambulant patients aged 18 years and above at the time of screening and able to walk 150 m in the 6-min Walking Distance Test (6MWD); women of child-bearing potential must be willing to use a contraceptive during the study; there must be prior paralytic poliomyelitis with evidence of motor neuron loss. This is confirmed by history of the acute paralytic illness, signs of residual muscle weakness and atrophy on neuromuscular examination, and signs of motor neuron loss.

A period of partial or complete functional recovery after acute poliomyelitis, followed by an interval (usually 15 years or more) of stable neuromuscular function is required and a slowly progressive and persistent new muscle weakness or decreased endurance, with or without generalised fatigue, muscle atrophy or muscle and joint pain must be demonstrable. Symptoms must have persisted for at least 1 year. Patients with other neuromuscular, medical and skeletal abnormalities causing the symptoms are excluded.

### Exclusion criteria

Excluded are patients those who have previously (3 months or less) or concomitantly participated in any other therapeutic trial; the use of CIT or L-arginine within the last 3 months; a known individual hypersensitivity to CIT; a known or suspected malignancy; any other chronic disease or clinically relevant limitation of renal, hepatic or cardiac function at the discretion of the investigator; pregnant or breast-feeding women and patients with severe renal failure (calculated glomerular filtration rate <30 ml/min).

### Randomisation and blinding

Patients who meet the study admission criteria are enrolled in the study and a single subject identification number will be assigned. Patients are allocated to the two study groups, CIT or placebo, in a 1:1 ratio. The trial is double blind, with both patients as well as the investigators assessing outcomes blinded to treatment allocation. Dropouts after visit 3 (week 24) will not be replaced.

### Intervention

All patients will undergo a 6-month observational (untreated) period to observe the natural history of their condition. Afterwards, they will be randomised into a verum or a placebo (1:1) group. All patients randomised to the active compound receive a daily dose of 15 g CIT (Hänseler AG, Herisau, Switzerland) separated in three doses per day (3 × 5 g). The patients randomised to the placebo group will receive matching placebo (sachets look like verum but contain mannitol). Treatment is given for a period of 24 weeks. At baseline (visit 2), week 24 (visit 3) as well as at the end of the study (visit 5), clinical measures, laboratory and magnetic resonance imaging (MRI) measures will be performed. This includes the 6MWD, the Motor Function Measurement (MFM) scale, quantitative motor tests (QMT), motor function assessment using quantitative thigh muscle MRI, and magnetic resonance (MR) spectroscopy and laboratory blood analysis. Furthermore, assessments concerning quality of life and impairments concerning daily activities are done with standardised questionnaires (SIPP – Self-reported Impairments in Persons with late effects of Polio, IBM-FRS – Inclusion Body Myositis Functional Rating Scale; WHOQOL – The WHO Quality of Life – BREF Questionnaire). A flow chart showing the study design is provided in Fig. 1.

**Fig. 1 Fig1:**
[figure not shown]
Flow chart showing the study design

To compare results of quantitative muscle MRI (Iterative Decomposition of water and fat with Echo Asymmetry and Least-squares estimation-Carr-Purcell-Meiboom-Gill (IDEAL-CPMG) with T_2_ and lipid quantitation and dynamic ^31^P-MR spectroscopy), motor function and serum markers of muscle necrosis, oxidative and nitrosative stress with an age- and gender-correlated group of people, up to 20 subjects not suffering from neuromuscular disorders will be included into a healthy control group. In this population, the 6MWD, MFM scale, QMT, quantitative MRI and MR spectroscopy and a blood test will be performed at a single time point.

### Study procedure

At screening (visit 1, day −1), patients are informed about preclinical data, alternative treatments, risks and possible benefits of the study. Further, written informed consent is obtained. After signing the Informed Consent Form, inclusion and exclusion criteria are verified. If the criteria are fulfilled, the patient will be enrolled in the study. During the screening visit, the following procedures are performed: 6MWD; vital signs; physical examination; MFM scale. After screening, four visits will be scheduled at baseline (week 0, visit 2), week 24 (visit 3), week 36 (visit 4) and week 48 (visit 5, end of study).

During visit 2 (week 0, baseline), the following procedures are performed: check inclusion/exclusion criteria; vital signs; physical examination; self-report questionnaires; muscle MRI; adverse events; blood draw (laboratory analysis) and urine pregnancy test in women of child-bearing potential. If the patient still qualifies for the study, they will be definitively enrolled in the study. Two weeks after screening, self-report questionnaires are filled in a second time by patients to evaluate the questionnaires for test-retest reliability. During visit 3 (week 24), the following procedures will be performed: 6MWD; vital signs; physical examination; self-report questionnaires; MFM scale; QMT; muscle MRI; adverse events; blood draw (laboratory analysis) and urine pregnancy test in women of child-bearing potential. If the patient still qualifies for the study, they will be randomised and receive the study medication or placebo accordingly. During visit 4 (week 36), the following procedures are performed: 6MWD; vital signs; physical examination; MFM scale; QMT adverse events; blood draw (laboratory analysis); dispensing of study medication; collection of boxes with sachets of used study medication for compliance control. During the last visit (visit 5, week 48, end of study), the following procedures are performed: 6MWD; vital signs; physical examination; self-report questionnaires; MFM scale; QMT; muscle MRI; adverse events; blood draw (laboratory testing); collection of boxes with sachets of used study medication for compliance control. The full planned visiting and examination schedule is provided in Fig. 2.

**Fig. 2 Fig2:**
[figure not shown]
Planned visiting and examination schedule *will be used as baseline values. Vital signs include: blood pressure, heart rate, weight at every visit; height only at screening visit. Motor Function Measurement (MFM) scale, 6-min Walking Distance Test (6MWD), quantitative motor tests (QMT), and screening will be used as baseline values. Full blood count: erythrocytes, reticulocytes, leucocytes, platelets, haemoglobin, haematocrit. GOT, GPT, creatinine, electrolytes (Na^+^, K^+^, Ca^2+^), urea, creatine kinase (CK), glycosylated haemoglobin (HbA1c), cholesterol, high-density lipoprotein (HDL), low-density lipoprotein (LDL), triglycerides, calculated glomerular filtration rate (GFR). Oxidised DNA (8-hydroxy-2’-deoxyguanosine: 8OHDG), carbonylated proteins (4-Hydroxynonenal (4-HNE)), mitochondrial proteins (citratsynthase, cytochrome C oxidase subunit 1, succinate dehydrogenase subunit A), nitrotyrosine, cGMP. Woman of child-bearing potential. SIPP – Self-reported Impairments in Persons with late effects of Polio, IBM-FRS – Inclusion Body Myositis Functional Rating Scale, WHOQOL-BREF – The WHO Quality of Life – BREF Questionnaire

### Quality assurance

To assess high-quality conduct of the trial in accordance with the protocol, all medical staff involved in this study are certified in Good Clinical Practice (GCP). The physiotherapists who perform the tests were trained and certified in Lyon where the MFM scale has been established and validated. To assess compliance of medication intake, empty and full boxes with sachets are returned by the patients at visits 4 and 5.

Allocation concealment is assured by an unblinded pharmacist who has access to the randomisation list. The investigator and the participants stay blinded until the end of the study.

### Safety assessments

Adverse events are monitored throughout the study. At every study visit, patients are asked about adverse events. At visits 1, 3, 4 and 5, a physical examination will be performed and the vital parameters will be measured. The following safety parameters are checked: full blood count; blood chemistry (transaminases, creatinine, electrolytes, urea); marker of muscle necrosis (creatine kinase concentration); serum markers of oxidative stress (8-hydroxy-2’-deoxyguanosine (8OHDG), carbonylated proteins); serum markers of nitrosative stress (nitrotyrosine, cGMP); all amino acids; glucose metabolism marker (HbA1c); lipid metabolism markers (cholesterol, high-density lipoprotein (HDL), low-density lipoprotein (LDL), triglycerides). If pathological changes independent of the known muscle disease should be detected, the affected patients will be informed immediately and the possibilities of further investigation or treatment of these abnormalities according to current medical knowledge, respectively, will be discussed.

Withdrawal of consent, protocol violations caused by the patients (noncompliance), logistical reasons, inability to attend study visits as defined in the protocol, abnormal laboratory results and abnormal increase in blood pressure as determined by the investigator can lead to an early termination of the study. Patients with adverse reactions which have occurred in context of the study are followed up by the investigator up to 30 days after the last visit. Serious adverse events will be reported within 7 days (after being reported by the patient) to the local national Ethics Committee. Female patients of child-bearing age will be instructed to use a double-barrier method of birth control and to immediately inform the investigator if they become pregnant during the study. The study drug is discontinued at the discretion of the investigator.

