### Outcome measures

#### Primary outcome measure

##### Change of 6MWD from week 24 to week 48 under L-citrulline therapy versus placebo

Several tests have been reported in the medical literature to assess muscle strength and functional ability, to monitor the progression of the disease, and to evaluate the results of drug interventions and rehabilitation. Timed clinical functional assessments include the 6-min Walking Distance Test (6MWD) in meters which is helpful to assess muscle function and fatigue in patients with neuromuscular disorders [16, 17]. The 6MWD is a validated tool to measure the distance that an individual is able to walk over a total of 6 min on a hard, flat surface. The goal for the individual is to walk as far as possible in 6 min. The individual is allowed to self-pace and rest as needed as they traverse back and forth along a marked walkway.

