### Statistics

The full analysis set (FAS) consists of all patients who are randomised and for whom a baseline measurement of the primary endpoint is available. The intention-to-treat (ITT) set is a subset of the FAS that consists of all patients for whom there is a follow-up measurement of the primary endpoint. According to the ITT principle, each patient will be analysed according to the treatment that they are randomly allocated to. The per-protocol (PP) set is a subset of the ITT set that consists of all patients with complete follow-up measurements of the primary endpoint. Each patient will be analysed according to the treatment that they actually receive.

An ANCOVA will be used for the primary analysis. The response variable is the 6MWD after the 24-week treatment period (follow-up). The explanatory variables are the 6MWD at the onset of the treatment period (baseline) and the group (placebo versus verum). The model estimates will be presented together with 95% confidence intervals and *p* values with respect to the null hypothesis that the corresponding estimate has a value of 0. The analysis will be performed on the ITT set. The analysis will be repeated on the PP set and compared to the ITT analysis as a sensitivity analysis.

Following the analysis of the primary endpoint, the secondary endpoints will be analysed as outlined above for the primary endpoint.

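### Noncompliance, laboratory and blood-pressure findings can end a patient's study participation, not only study drug, so randomised patients who still consent may have no week-48 walk and leave the primary analysis

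*Protocol article*

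**What the plan says.** The Safety assessments section puts several grounds in one sentence. It begins "Withdrawal of consent, protocol violations caused by the patients (noncompliance), logistical reasons, inability to attend study visits as defined in the protocol" and continues "abnormal laboratory results and abnormal increase in blood pressure as determined by the investigator can lead to an early termination of the study". Later in the section, a separate sentence reads "The study drug is discontinued at the discretion of the investigator".

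The primary outcome is "Change of 6MWD from week 24 to week 48 under L-citrulline therapy versus placebo". Under Statistics, the ANCOVA response is the walk after the 24-week treatment period. The ITT set "is a subset of the FAS that consists of all patients for whom there is a follow-up measurement of the primary endpoint", and the primary analysis is run on it. The same section states: "According to the ITT principle, each patient will be analysed according to the treatment that they are randomly allocated to". The per-protocol (PP) set, used for the only sensitivity analysis named, is a subset of the ITT set.

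Randomisation and blinding adds "Dropouts after visit 3 (week 24) will not be replaced". Ethical considerations provides one last safety examination after withdrawal and the use of data gathered up to that point. It does not mention a 6MWD at that examination or attendance at week 48.

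**The concern.** Withdrawal of consent ends data collection, and a patient who cannot attend cannot be walked. Noncompliance, a laboratory abnormality and a rise in blood pressure are different. They arise after randomisation, treatment may affect them, and the patient may be willing and able to walk at week 48. If such a patient is ended from the study, the missing outcome follows from a rule in the plan rather than from necessity.

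The laboratory ground shows the link to treatment. The article does not say which results count as abnormal for this purpose. Its list of safety parameters includes creatine kinase, nitrotyrosine and cGMP, and the secondary-outcome section names these among the markers the treatment is meant to influence.

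What is at stake is the comparison of the groups as randomised. An analysis plan can model or impute a missing walk, but it cannot supply one that was not measured.

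**Working it through.** **1. Does the rule end participation or only medication?** The grounds are patient-level, the stated consequence is termination of the study, and stopping drug has its own sentence. The natural reading is that the patient leaves the study. The wording is permissive (can lead to), so this is something the plan allows, not something it requires.

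**2. When can it cost the endpoint?** From the Study procedure section:
- Visit 3 (week 24): bloods and vital signs are taken before randomisation, so a finding there precedes allocation.
- Visit 4 (week 36): first on-treatment bloods, vital signs and sachet return. A 6MWD is also done.
- Visit 5 (week 48): the primary walk is due at the same visit.

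Visit 4 is therefore the only scheduled check between randomisation and the endpoint, 48 − 36 = 12 weeks before it. Adverse events are monitored throughout, so an unscheduled finding is possible.

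**3. What happens in the analysis?** No week-48 walk means no response value for the ANCOVA. The patient falls outside the ITT set if follow-up means the post-treatment walk, as the response definition implies. The PP set, being smaller, cannot bring the patient back.

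**4. The plan's own dropout figure.** 25 evaluable / (1 − 0.10) = 27.8, rounded up to 28, as stated. With 30 planned, a 10% loss leaves 30 × 0.9 = 27, and 30 − 25 = 5 patients (16.7%) can be lost before the evaluable number falls below 25. The margin protects precision. It does nothing about selective loss.

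**5. Hypothetical size.** Inputs: 15 per arm (Randomisation scheme) and a 25% verum gain (Sample size estimation). Assume m verum patients with zero gain are lost, none are lost on placebo, and the retained verum patients average 25%. The mean over all randomised to verum is 25 × (15 − m)/15:
- m = 1: 23.3%, overstated by 1.7 points
- m = 2: 21.7%, overstated by 3.3 points
- m = 3: 20.0%, overstated by 5.0 points

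**6. Hypothetical effect on the test.** Assumed: no true effect, 15 per arm, standard normal residuals, a two-sided 5% t-test in place of the ANCOVA, losses on verum only, 40,000 simulated trials. The nominal rate favouring verum is 2.5%.

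| Verum patients lost | Shift (residual SD) | Two-sided rejection | Favouring verum |
|---|---|---|---|
| 1 at random from lowest 7 | 0.06 | 4.9% | 3.3% |
| 2 at random from lowest 7 | 0.13 | 5.8% | 4.8% |
| 3 at random from lowest 7 | 0.20 | 7.4% | 6.8% |
| worst 1 | 0.12 | 6.9% | 5.5% |
| worst 2 | 0.23 | 10.9% | 10.1% |
| worst 3 | 0.33 | 15.8% | 15.4% |

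By symmetry, the same losses on placebo give the same shifts with the sign reversed.

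**The case against.** The strongest reply is that the exposure is narrow and the harm unproven. Much of this stands.

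- **Narrow window.** Step 2 confirms that visit 4 is the main point of risk. A 6MWD is done there, and since the PP set asks for complete follow-up measurements, the ITT set might be read as admitting a patient with only a week-36 walk. That reading does not rescue the patient: the ANCOVA response is the walk after 24 weeks of treatment, and week 36 is 12 weeks into treatment.
- **On-treatment comparison.** A reader might infer that the primary analysis becomes an on-treatment comparison. The documents do not support this. Termination is optional, patients who stop drug are not said to leave follow-up, and everyone in the set is analysed as allocated.
- **Difference by arm.** A reader might infer that losses will differ by arm. Patients and outcome-assessing investigators are blinded, and no rate or direction is given. Blinding does not exclude a difference, because treatment could itself alter adherence, laboratory values or blood pressure. It remains possible, not shown.
- **Magnitude.** The figures in steps 5 and 6 put every loss on verum and make the lost patients poor responders. Three losses are 20% of one arm, twice the planned 10% rate, though only 3/30 = 10% of the trial. In the milder scenario, one or two losses leave two-sided rejection close to 5%.
- **Condensed article.** The full protocol may ask such patients back. That would answer the point, but the termination rule and the analysis set are both stated here, and as stated they combine to lose the patient.

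**Conclusion.** The point holds in a limited form. The stated termination grounds and the stated ITT definition together allow randomised patients who still consent to be lost from the primary analysis for post-randomisation reasons that treatment may affect, and no analysis named in the article recovers them. This rests on reading early termination as the end of the patient's participation, which the separate drug-discontinuation sentence supports.

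The size and direction of any bias are unknown. The 1.7 to 5.0 point overstatement illustrates one direction under chosen assumptions, and selective loss on placebo could understate the effect instead. A reader might take 1.7 points per lost patient as an expected inflation, but the article contains nothing from which such an expectation could be derived. Nor does each loss put the planned precision at risk, since 30 are planned against 25 evaluable. The matter is still worth correcting: with 15 per arm a few selective losses can matter, and the remedy is simple.

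**What to change.** In Safety assessments, separate stopping study medication from leaving the study. For noncompliance, laboratory or blood-pressure reasons, and for logistical reasons where attendance is possible:
- ask patients who still consent to attend the scheduled visit 5 for the week-48 6MWD;
- record the date and the reason medication stopped;
- include the value in the primary ANCOVA as randomised.

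Withdrawal of consent and true inability to attend will still leave gaps. The clinical reasons for stopping medication stay unchanged and are not judged here.

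The cost is a wording change to the protocol, plus attendance at a visit already in the schedule. The downside is small: some walks will be made off treatment and will dilute the estimated effect, which is what an analysis by randomised group accepts.
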